#### Primary outcome

2.4.1

The primary outcome measure is the change in global cognitive function from baseline (T0) to post-intervention (T1), assessed using the Montreal Cognitive Assessment (MoCA). The MoCA is a highly sensitive, 30-point screening tool specifically designed to detect mild cognitive impairment (MCI), assessing multiple cognitive domains including executive function, visuospatial ability, memory, attention, and language (Nasreddine et al., 2005). To determine the clinical relevance of any observed changes, we will apply a Minimal Clinically Important Difference (MCID) threshold. Based on recent clinimetric evaluations in older adults with cognitive impairment, an increase of ≥ 2 points on the MoCA will be considered a clinically meaningful improvement (Lindvall et al., 2024).

While the MoCA is less susceptible to ceiling effects than the Mini-Mental State Examination (MMSE) in MCI populations, some participants with very mild impairment (e.g., baseline scores of 24–25) may still approach the maximum score of 30, potentially masking further cognitive gains (Trzepacz et al., 2015). To mitigate this, our statistical analysis plan will incorporate Tobit regression models, which are specifically designed to handle censored data and adjust for potential ceiling effects, ensuring accurate estimation of the intervention’s true cognitive impact (Proust-Lima et al., 2007).

#### Secondary outcomes

2.4.2

Secondary outcomes encompass specific cognitive domains, physical performance, and quality of life, all measured at T0, T1, and T2. Memory will be assessed using the Wechsler Memory Scale, Fourth Edition (WMS-IV), while executive function will be evaluated via the Trail Making Test (Parts A and B). Physical performance will be measured using the 6-Minute Walk Test (6MWT) to assess functional exercise capacity and the Berg Balance Scale (BBS) to evaluate static and dynamic balance. Finally, quality of life will be assessed using the 12-item Short Form Health Survey (SF-12).

#### Neurophysiological biomarkers

2.4.3

To objectively quantify changes in neuroplasticity and cognitive processing speed, the P300 event-related potential (ERP) will be recorded using electroencephalography (EEG) at baseline (T0) and post-intervention (T1). The P300 component will be elicited using a standardized two-stimulus auditory oddball paradigm, in which participants are instructed to press a button in response to an infrequent target tone (e.g., 2000 Hz, 20% probability) embedded within a series of frequent standard tones (e.g., 1000 Hz, 80% probability) (Costanzo et al., 2024).

The P300 is a robust, non-invasive biomarker of attention and working memory updating. In individuals with MCI, the P300 typically exhibits reduced peak amplitude and prolonged latency compared to healthy age-matched controls, reflecting slowed neural processing and reduced allocation of attentional resources (Demirayak et al., 2023). We will specifically analyze the P300 peak latency (in milliseconds) and peak amplitude (in microvolts) at midline electrodes (Fz, Cz, Pz), where the signal is most prominent. A reduction in P300 latency and an increase in amplitude post-intervention will serve as direct neurophysiological evidence of enhanced cortical efficiency and target engagement by the iTBS and dance interventions (Stuckenschneider et al., 2020).

#### Exploratory outcome measure

2.4.4

Resting-state functional connectivity (rs-fMRI). To investigate the underlying neuroplastic mechanisms of the interventions, resting-state functional magnetic resonance imaging (rs-fMRI) will be acquired at T0 and T1. Analysis will focus on changes in functional connectivity within the Default Mode Network (DMN) and frontoparietal networks. rs-fMRI provides a task-free, low-burden method to quantify network-level neuroplasticity induced by iTBS and dance interventions in older adults with MCI (Balazova et al., 2021; H. Zhang et al., 2019).

### Qualitative interviews (acceptability and feasibility)

2.5

To comprehensively understand the intervention’s acceptability, feasibility, and perceived impact, a qualitative component will be embedded within the randomized controlled trial. This mixed-methods approach will provide rich, in-depth insights that complement the quantitative outcome measures.

#### Participants and sampling

2.5.1

A purposive sample of approximately 20–25 participants (5–7 from each intervention group, including the control group) will be recruited for individual semi-structured interviews. This sampling strategy will ensure representation across intervention arms and varying levels of engagement and outcomes. Additionally, 5–7 medical staff (e.g., neurologists, nurses, rTMS technicians, dance instructors) involved in the study will be interviewed to gather perspectives on implementation feasibility, challenges, and perceived benefits.

#### Data collection

2.5.2

Individual semi-structured interviews will be conducted by a trained qualitative researcher (not involved in direct participant care or intervention delivery) at the end of the 12-week follow-up period (Week 24). Each interview is expected to last approximately 45–60 minutes. Interviews will be audio-recorded with explicit consent and transcribed verbatim. The interview guides will be developed based on relevant literature and the study objectives. For Participants: Acceptability of the intervention (e.g., comfort, enjoyment, perceived burden), satisfaction with the program, perceived cognitive and physical changes, social engagement, and suggestions for improvement. For Medical Staff: Feasibility of implementing the rTMS and dance interventions (e.g., logistical challenges, resource requirements, training needs), perceived participant engagement and response, and overall impressions of the program’s integration into clinical practice.

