### Participants

2.2

Participants will be recruited from the Department of Rehabilitation at Handan Central Hospital. A convenience sampling method will be employed, with local physicians providing a list of potentially eligible patients diagnosed with MCI. All participants will provide written informed consent before enrollment. A family member or legal guardian will also be asked to co-sign the consent form. Participant data will be anonymized to ensure confidentiality. The data will be secured during the study and destroyed five years after the study completion.

Inclusion criteria: (1) Diagnosis of amnestic or multi-domain MCI by a specialist physician according to the National Institute on Aging-Alzheimer’s Association (NIA-AA) criteria. (2) Age between 50 and 85 years. (3) Montreal Cognitive Assessment (MoCA) score between 18 and 25. (4) Geriatric Depression Scale (GDS-15) score < 5. (5) Physically able to participate in dance activities without assistive devices and deemed at low risk for falls (Berg Balance Scale score ≥ 41). (6) Stable doses of any prescribed medications for at least 30 days prior to screening. (7) Sufficient visual and auditory acuity (with correction if necessary) to complete assessments and interventions. (8) Voluntarily agrees to participate and provides informed consent.

Exclusion criteria: (1) Diagnosis of dementia (any type). (2) Presence of major psychiatric conditions (e.g., major depressive disorder, schizophrenia) or neurological disorders (e.g., Parkinson’s disease, stroke) that could confound cognitive assessment. (3) Contraindications to rTMS (e.g., history of seizures, metallic implants in the head). (4) Regular participation in structured exercise (≥ 3 times per week) or another cognitive intervention program within the past six months. (5) Abuse of drugs or alcohol that could cause cognitive impairment.

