### Intervention protocol

2.3

The study consists of a 12-week intensive intervention phase followed by a 12-week follow-up phase. This 12-week duration is chosen based on evidence that significant cognitive and neuroplastic changes in MCI populations typically manifest within 3 months of rTMS and structured exercise (e.g., dance) (Guo et al., 2025; Sánchez-Alcalá et al., 2025). While a 24-week intervention was considered, the 12-week model is preferred to maximize participant retention and minimize “intervention fatigue” in this elderly population, while still being sufficient to demonstrate synergistic effects (Ren et al., 2025). The subsequent 12-week follow-up will allow for the assessment of the durability of these effects—a critical factor for clinical translation. Participants will be supervised by trained instructors and medical staff.

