### Measurement outcomes

2.4

Assessments will be conducted at three time points: Baseline (T0), Post-Intervention (T1, Week 12), and Follow-up (T2, Week 24). T1 assessments will be conducted 24–72 hours after the final intervention session of Week 12, to avoid the potential confounding influence of acute rTMS and dance exposure on cognitive and physical performance. To control for circadian variation, T1 and T2 assessments for each participant will be scheduled at the same time of day as that participant’s T0 assessment. Participants’ self-rated scales will be completed under guidance. All the tests will be administered in accordance with the standard procedures. The specific schedule of enrolment, interventions, and assessments is detailed in **Table 1**.

**Table 1 T1:** SPIRIT schedule of enrolment, interventions, and assessments.

Procedure	*Enrolment*	*Allocation*	*Intervention Phase*	*Post-Intervention*	*Follow-up*
*Timepoint*	-t_1_ (Screening)	T0 (Baseline)	Weeks 1–12	T1 (Week 12)	T2 (Week 24)
Enrolment:					
*Eligibility Screening*	**X**				
*Informed Consent*	**X**				
*Demographics & Medical History*	**X**				
*Inclusion MoCA, GDS-15, BBS*	**X**				
*Randomization*		**X**			
Interventions:					
*Active or Sham iTBS (rTMS)*			**X**		
*Chinese Square Dancing (DMI)*			**X**		
*Social Activity Control*			**X**		
Assessments:					
Primary outcome					
*Montreal Cognitive Assessment (MoCA)*		**X**		**X**	**X**
Secondary outcomes					
*Wechsler Memory Scale (WMS-IV)*		**X**		**X**	**X**
*Trail Making Test (Part A & B)*		**X**		**X**	**X**
*Berg Balance Scale (BBS)*		**X**		**X**	**X**
*6-Minute Walk Test (6MWT)*		**X**		**X**	**X**
*12-item Short Form Survey (SF-12)*		**X**		**X**	**X**
Neurophysiological & exploratory					
*EEG/ERP (P300 Oddball paradigm)*		**X**		**X**	
*Resting-State fMRI (rs-fMRI)*		**X**		**X**	
Safety & fidelity					
*Adverse Events Monitoring*			**X**	**X**	
*Blinding Integrity Questionnaire*				**X**	
*Qualitative Interviews*					**X**

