### Sample size

2.7

A priori power analysis (G*Power 3.1) was conducted for a four-group repeated measures ANOVA (interaction effect). To detect a medium effect size (f = 0.25) with a power of 0.8 and an alpha level of 0.05, a total sample of approximately 128 participants (32 per group) is required. To account for potential participant dropouts, we have factored in an anticipated attrition rate of 20% over the 24-week study period (12-week intervention plus 12-week follow-up). This 20% estimate is intentionally conservative and rigorously justified by previous longitudinal literature involving older adults with cognitive impairment. Systematic reviews of intensive, multi-modal non-pharmacological interventions (including aerobic exercise and neuromodulation protocols) in geriatric populations consistently report attrition rates ranging from 15% to 21%, typically due to transportation barriers, intervention fatigue, or unrelated emergent health issues (Di Lorito et al., 2020). Therefore, to ensure the trial remains adequately powered throughout the follow-up phase, we aim to recruit a final total of 160 participants (40 per group).

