#### Mixed-methods data integration

2.9.3

To maximize the explanatory power of this study, the integration of quantitative and qualitative data will occur at the interpretation phase using an embedded mixed-methods framework. Rather than analyzing the data streams in isolation, the qualitative findings will be systematically used to contextualize, explain, and expand upon the quantitative results. For example, if the quantitative linear mixed-effects models reveal that the Combined Intervention group achieves high clinical efficacy but suffers from unexpectedly low adherence or high attrition rates, the qualitative data will be crucial in identifying the underlying mechanisms—such as the perceived logistical or physical burden of attending both the iTBS and dance sessions. Conversely, if specific cognitive domains (e.g., executive function) show significant improvement, the interview transcripts will be analyzed to uncover the specific components of the DMI or social interactions that participants felt contributed most to those gains. This synergistic integration will provide a comprehensive understanding of not just *whether* the intervention is effective, but *how* and *why* it works, thereby yielding highly actionable insights for future real-world clinical implementation.

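### Participant interviews held only at Week 24 are poorly placed to explain low adherence or attrition, and are prone to recall and survivor bias

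*Protocol article*

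**What the plan says.** Section 2.5.2 (Data collection) places the individual interviews "at the end of the 12-week follow-up period (Week 24"). Table 1 agrees: the row "Qualitative Interviews" is marked only in the T2 column. Section 2.3 gives the timeline: "The study consists of a 12-week intensive intervention phase followed by a 12-week follow-up phase". Participant topics include comfort, enjoyment, burden, satisfaction and perceived change.

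Respondents meet the inclusion criterion "Diagnosis of amnestic or multi-domain MCI by a specialist physician" (section 2.2). Section 2.5.1 plans about 20 to 25 participant interviews, 5 to 7 per group, chosen purposively to cover a range of engagement and outcome, plus 5 to 7 staff interviews.

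Section 2.9.3 gives the interviews an explanatory task. If the Combined group does well clinically but "suffers from unexpectedly low adherence or high attrition rates, the qualitative data will be crucial in identifying the underlying mechanisms", with the burden of attending both modalities given as an example. Section 2.7 assumes "an anticipated attrition rate of 20% over the 24-week study period (12-week intervention plus 12-week follow-up") and describes the losses as "typically due to transportation barriers, intervention fatigue, or unrelated emergent health issues".

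**The concern.** The plan expects some people to leave for reasons the interviews are meant to uncover, intervention fatigue and transport among them. It then schedules the only participant interview at the last study time point, when most of those people will have gone. Those who remain are asked about the burden of a programme that ended 12 weeks earlier, and they have a condition in which delayed recall is a foreseeable weakness.

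At stake is the credibility of the acceptability and feasibility findings, and of any account of why people stopped or attended poorly. The conclusions section aims at a feasible strategy that could inform guidelines. If the evidence comes mainly from people who stayed, that aim is exposed to bias, and the missing accounts may be hard to recover afterwards.

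**Working it through.** **Inputs.** Planned total 160, 40 per group; required number before losses 128; attrition 20%, with a cited range of 15% to 21% (all section 2.7). Sessions end at Week 12 (section 2.3). The 5-days-a-week stimulation phase ends at Week 4 (section 2.3.1). Interviews are at Week 24 (section 2.5.2, Table 1).

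**1. The plan's own figure.** 128 / (1 − 0.20) = 160. The recruitment target reproduces, so the 20% can be used as the plan's working assumption.

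**2. Expected losses by Week 24.**
- At 20%: 0.20 × 160 = 32 in total; 0.20 × 40 = 8 per group if losses are even.
- At 15%: 0.15 × 160 = 24.
- At 21%: 0.21 × 160 = 33.6, about 34.

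The article does not split losses before and after Week 12, or by reason. The number who left because of the treatment is therefore unknown.

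**3. Recall interval at the interview.**
- From the last session: 24 − 12 = 12 weeks.
- From the end of the intensive stimulation phase: 24 − 4 = 20 weeks.
- From the first sessions: up to about 24 weeks.

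An interview at Week 12 would still be 12 − 4 = 8 weeks after the intensive phase. Moving the date shortens recall but does not remove it.

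**4. Low adherers.** Section 2.2 lists missing more than six sessions without the possibility of making them up, and not following instructions, among the events that end participation. Some of the poorest attenders, and not only those who choose to leave, may therefore be gone by Week 24.

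**5. What the other sources supply.**
- *Purposive sampling (2.5.1)* seeks a range of engagement and does not exclude people who stopped. The article states no time point other than Week 24 at which to reach them.
- *Staff interviews (2.5.1, 2.5.2)* cover logistics and observed engagement. Section 2.6.3 uses them to triangulate participants' accounts, and they are second-hand on personal burden.
- *The session log (2.3.2)* is contemporaneous but covers the dance sessions only. It records attendance, active time, engagement rating, posture and adverse events. Reasons for absence, perceived burden and stimulation visits are not listed.
- *Returning transcripts to participants (2.6.3)* checks that the transcript is right, not that the memory is.

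Each source narrows the gap. None supplies a first-hand account from people who stopped, given near the time they stopped.

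**The case against.** The strongest reply is that the timing is a defensible choice with trade-offs. Explaining attrition is a conditional example in section 2.9.3. The component's stated aims are acceptability, feasibility and perceived impact, and perceived impact after follow-up suits Week 24. Participants have MoCA scores of 18 to 25 and no dementia, and are asked for general impressions of repeated sessions, not for detailed episodes. Retained participants with patchy attendance can still describe burden. Sampling on outcomes needs Week 12 results in hand. Week 12 already carries a heavy battery, including EEG, fMRI and a blinding questionnaire. A long discussion of benefit before Week 24 could colour later self-report. A condensed article may also leave procedures for contacting leavers to the full protocol.

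Much of this stands. A reader might infer that the interviews cannot explain adherence or attrition at all. The documents do not support that, because leavers are not excluded, staff are interviewed and a log exists. A reader might also set 32 leavers against 20 to 25 interviewees as a measure of the bias. It is not one: a purposive sample is not a fraction of the dropouts. Nor do the documents establish the size or direction of any bias, although a favourable lean is plausible. Describing the cohort as selected for memory impairment is only approximate, since the criterion is amnestic or multi-domain impairment.

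The objection does not remove the mismatch between a stated time point and a stated use. The point rests on the Week 24 schedule in the text and in Table 1, not on a detail the article left out.

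**Conclusion.** The point holds in a limited form. Interviewing participants only at Week 24 is a poor fit for explaining low adherence or attrition, and brings avoidable recall and survivor bias to the acceptability and feasibility findings. The affected group is about 32 of 160 participants (24 to 34 over the cited range), and recall is at least 12 weeks. This assumes that the plan's attrition figure is right, that most people who leave are not in practice interviewed at Week 24, and that no exit interview is arranged in a document not shown. The arithmetic sizes the group at risk of being missed; it does not measure the bias. The primary endpoint, the change in MoCA from baseline to Week 12, is unaffected. The change is worth making, but no efficacy conclusion depends on it.

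**What to change.** **Main change.** Within the existing 5 to 7 interviews per arm, reserve 1 or 2 for participants who discontinue early. The same independent interviewer would see them at their last visit, or telephone them, when they stop. State this in sections 2.5.1 and 2.5.2 and in Table 1. Across four arms this is 4 to 8 places, with no added interviews or staff. Section 3.7.3 already separates withdrawal from the trial and withdrawal from the interview, so the arrangement fits the consent model. The additional interview consent in section 3.7.2 would have to be obtained at that point.

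**Preferred addition.** Hold the remaining interviews soon after the Week 12 assessments are complete, on a separate day and once the results allow sampling on outcomes. Add a few short questions on lasting effects after the Week 24 assessments. This shortens recall and reaches people lost between Weeks 12 and 24. It does not reach those who left during treatment, which is why the reserved places matter more.

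**Cost.** Amended text, Table 1 and consent wording, and some extra scheduling. Between 3 (5 − 2) and 6 (7 − 1) interviews per arm remain for completers. If the interviews move to Week 12, interviewed participants discuss perceived benefit before the Week 24 self-report; section 2.10 treats Week 24 durability and SF-12 as supportive or exploratory, which limits the harm. If the sponsor keeps Week 24 for completers, the early-stopper interviews alone still address the survivor bias, and the recall limitation should be acknowledged.

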#### Reporting

2.5.3

The qualitative findings will be reported in accordance with the Consolidated Criteria for Reporting Qualitative Research (COREQ) 32-item checklist (Tong et al., 2007).

### Measures to ensure reliability and validity

2.6

To ensure the highest level of scientific rigor, this study incorporates robust measures to protect both the internal and external validity of the quantitative data, as well as the trustworthiness of the qualitative findings.

#### Quantitative reliability and validity

2.6.1

To ensure the validity of the clinical data, all selected primary and secondary outcome measures (e.g., MoCA, WMS-IV, BBS, 6MWT) are highly standardized, widely validated, and culturally adapted for older Chinese populations with MCI. To maximize inter-rater reliability, all outcome assessors will undergo intensive pre-trial training and standardization sessions to ensure absolute consistency in test administration and scoring.

To minimize detection bias, the trial employs strict single-blinding; outcome assessors will remain completely blinded to participant group allocation across all time points (Baseline, Week 12, Week 24). Furthermore, intervention reliability (treatment fidelity) will be maintained through standardized operating procedures (SOPs). For the rTMS protocol, neuronavigation will be utilized to guarantee precise and consistent targeting of the left DLPFC across all sessions. For the DMI, adherence to the choreographic protocol and targeted exertion levels (Borg Scale 4-6) will be continuously monitored by supervising medical staff.

#### Blinding integrity assessment

2.6.2

To rigorously evaluate the success of the single-blind design and ensure that treatment effects are not confounded by participant expectations, a formal assessment of blinding integrity will be conducted. At the conclusion of the 12-week intervention phase (T1), all participants will be asked to complete a standardized blinding questionnaire. Participants will be asked to guess their assigned intervention arm (e.g., “Active iTBS + Dance,” “Sham iTBS + Dance,” etc.) and to state the primary reason for their guess (e.g., perceived physical sensations, perceived cognitive improvement, or random guess) (Kolahi et al., 2009).

The blinding efficacy will be quantitatively evaluated using Bang’s Blinding Index (BBI), a validated statistical metric that ranges from -1 (complete opposite guessing) to 1 (complete unblinding), with 0 indicating perfect blinding (random guessing) (Bang et al., 2004). The BBI will be calculated separately for the active and sham iTBS conditions to determine if the sham coil successfully mimicked the somatic sensations of active stimulation without unmasking the participants (Berlim et al., 2013). If the BBI indicates significant unblinding, the participant’s guess will be included as a covariate in the secondary sensitivity analyses to adjust for potential expectancy biases.

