### Randomization-sequence generation and blinding

2.8

Participants will be randomly allocated to one of the four groups using a computer-generated randomization sequence. Allocation concealment will be ensured using sealed, opaque envelopes, which will be opened by a researcher not involved in assessment or intervention delivery. This is a single-blinded trial. Outcome assessors will be blinded to the group allocation of participants. Due to the nature of the interventions, participants and instructors cannot be blinded. However, participants will be instructed not to discuss their intervention with the assessors.

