##### Analysis of primary and secondary outcomes

2.9.1.2

To evaluate the individual and synergistic effects of the interventions across the three assessment time points (baseline, Week 12, and Week 24), linear mixed-effects models (LMMs) will be employed. LMMs are particularly well-suited to this trial design, as they accommodate repeated measures, account for intra-subject correlation, and appropriately handle missing data under the missing-at-random (MAR) assumption without necessitating listwise deletion. The outcome measures—including global cognitive function (MoCA), memory, executive function, EEG/ERP parameters, and physical performance metrics—will be modelled as dependent variables. Fixed effects will comprise Group (Combined Intervention, rTMS Only, DMI Only, Control), Time (T0, T1, T2), and the Group × Time interaction term, with the latter serving as the primary indicator of intervention efficacy over the study period. Participant identification will be specified as a random intercept to account for between-subject variability.

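### In the article's mixed model, the guess entered as a plain covariate cancels from the T0–T1 contrast, so the expectancy check cannot detect expectancy unless 2.6.2 names another model or a Time interaction

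*Protocol article*

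**What the plan says.** Protocol article, 2.6.2 (Blinding integrity assessment). The guess is collected once: "At the conclusion of the 12-week intervention phase (T1), all participants will be asked to complete a standardized blinding questionnaire". What is recorded is the whole arm: "Participants will be asked to guess their assigned intervention arm". Bang's index is calculated separately for the active and sham coil conditions. The adjustment is conditional, introduced by "If the BBI indicates significant unblinding", and consists of this: the participant's "guess will be included as a covariate in the secondary sensitivity analyses to adjust for potential expectancy biases". No model is named and no interaction with Time is mentioned.

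Protocol article, 2.9.1.2 to 2.9.1.4. The outcomes go into a linear mixed model whose fixed effects are Group, "Time (T0, T1, T2), and the Group × Time interaction term, with the latter serving as the primary indicator of intervention efficacy". The random part is a random intercept: "Participant identification will be specified as a random intercept to account for between-subject variability". The 2 × 2 factorial tests are nested within these models. Age, gender, education and baseline MoCA are added as covariates, with no Time interactions stated.

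Sections 2.4.1 and 2.10 define the primary outcome as the change in MoCA from T0 to T1.

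**The concern.** Expectancy created by treatment can act only after T0. A covariate that is constant within a person, entered as a main effect in a model with T0 among the outcomes, is forced to act equally at T0, T1 and T2. It can absorb a stable difference in level between people who guess active and people who guess sham. It cannot absorb a difference in their change, and the change is what the trial tests.

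This is the only expectancy-adjusted analysis the article states, and it is triggered only when unblinding has been found. An analysis that must return the unadjusted contrast gives no information at the point where it is needed. A reader who sees the two estimates agree would naturally take that as reassurance about the rTMS effect and about synergy.

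**Working it through.** The article gives no figure for this analysis, so there is none to reproduce. The design size used below is its own: 128 / (1 − 0.20) = 160, or 40 per arm (2.7).

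**Step 1, the algebra.** For person i at visit t, the model of 2.9.1.2 with the guess g added as a main effect is

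Y(i,t) = intercept + Group + Time(t) + Group × Time(t) + γ·g(i) + b(i) + error,

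where b(i) is the random intercept. Subtract T0 from T1:

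Y(i,1) − Y(i,0) = Time(1) + Group × Time(1) + error difference.

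Both γ·g(i) and b(i) drop out. The Group × T1 term is therefore the between-arm difference in mean change, whatever γ is. Age, gender, education and baseline MoCA entered as main effects cancel in the same way. With a guess × Time term, δ(1)·g(i) remains in the difference and can take up a belief effect.

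A guess exists only for people who complete the T1 questionnaire, so T0 and T1 should both be present for everyone in the adjusted analysis. Missing T2 scores then do not disturb the cancellation, because each group has its own free mean at each visit.

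**Step 2, the size of what is left in place.** Assumptions, not from the article: no true coil effect; believing the coil is active adds B = 1.5 MoCA points at T1 and T2; a proportion p guess their coil correctly in both the active and sham arms. Then

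spurious rTMS contrast = B × [p − (1 − p)] = 1.5 × (2p − 1).

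| p | 0.6 | 0.7 | 0.8 | 0.9 |
|---|---|---|---|---|
| Spurious contrast (points) | 0.3 | 0.6 | 0.9 | 1.2 |

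A spurious rTMS × DMI contrast arises if p differs between the dance and social arms. For example, 0.8 with dance and 0.6 without gives 0.9 − 0.3 = 0.6 points. The main-effect covariate leaves that in place too.

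**Step 3, simulation of belief-only effects.** 40 per arm, p = 0.8. SDs (between-person, residual) are assumed: 1.8 and 1.5 for B = 1.5; 2 and 1.5 for B = 2. Entries are the mean rTMS contrast at T1, with the share of trials at p < 0.05 where recorded.

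| Setting | No guess | Guess as main effect | Guess × Time |
|---|---|---|---|
| B = 1.5, complete, 60 trials | 0.96 (82%) | 0.96 (82%) | 0.04 (5%) |
| B = 1.5, 20% missing at T2 | 0.94 | 0.94 | 0.05 |
| B = 2, complete, 80 trials | 1.27 (95%) | 1.27 (95%) | 0.06 (7.5%) |
| B = 2, 20% dropout, some before T1, 60 trials | 1.172 (82%) | 1.174 (85%) | −0.05 (5%) |

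With complete data the largest change in any trial from adding the main effect was 3e-13, which is rounding error. The last row kept a guess even for people lost before T1. There the mean absolute shift was 0.008 and the largest 0.037, so the cancellation is then near-exact rather than exact.

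**Step 4, the models in which a plain covariate does work.** With B = 1.5, p = 0.8 and 400 simulated trials, an analysis of the T0–T1 change went from 0.93 to 0.00 when the guess was added (significant in 76% v 4.5%). An ANCOVA at T1 went from 0.92 to 0.01 (82% v 4.5%). The outcome therefore depends on which model 2.6.2 means.

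**The case against.** The strongest reply is that 2.6.2 names no model. The primary outcome is defined as a change, 2.10 analyses the key secondary outcomes as changes, and 2.9.1.4 adjusts for baseline MoCA, which is usual in a change or ANCOVA model. Under either of those the stated covariate works (step 4). If the rTMS main effect of 2.9.1.3 were read as an average over all three visits, the covariate would also move it: at p = 0.8 that average is (0 + 0.9 + 0.9)/3 = 0.6, and it fell to 0.01 in simulation. This stands as a limit. A reader might infer that the adjustment fails under any analysis, and the article does not support that. What it supports is narrower: the one model written out is the mixed model with T0 as an outcome, Group × Time is named there as the indicator of efficacy, and in it the stated adjustment does nothing to the T0–T1 contrast.

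A second reply is that such detail belongs in an analysis plan that is not shown. But the article does fix the form of the adjustment and its purpose, and in its own model that form cannot serve that purpose.

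A third is that the guess follows treatment, and 2.6.2 itself lists perceived cognitive improvement as a reason for guessing. An adjustment that reaches the contrast can therefore remove real benefit. In simulations with a true 2-point effect, no belief effect, and guesses driven by the person's own improvement, the adjusted estimate fell to 1.64 or 1.25, a loss of 18% or 38%. This stands too. It is a hazard of the article's own decision to adjust for the guess, and it governs how the result should be labelled.

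A reader might also infer that the four-level guess breaks the model, because dance status is known to the participant (2.8: "Due to the nature of the interventions, participants and instructors cannot be blinded"). If everyone reports dance status correctly, intercept + Group + arm guess does have rank 6 of 7. That affects only a DMI effect averaged over visits and cannot touch Group × Time. It is a reason to use only the coil part of the guess, nothing more.

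**Conclusion.** The concern holds in this form: with the guess as a main effect in the mixed model of 2.9.1.2 to 2.9.1.4, the expectancy analysis reproduces the unadjusted T0–T1 rTMS and rTMS × DMI contrasts, whatever the role of belief. The cancellation is algebraic when T0 and T1 are both present, and needs no assumed values. Apparent differences could still arise because people without a T1 questionnaire drop out of the adjusted analysis.

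The size is illustrative. Under the assumptions of step 2, 0.3 to 1.2 MoCA points would pass through unadjusted, against the 2-point threshold for meaningful improvement in 2.4.1. The article gives no basis for choosing a belief effect or guess rate within or beyond that range, so no single figure should be read as the expected bias. Nor does the article say that an unchanged estimate would be reported as robust; that is how agreement would tend to be read. The primary analysis itself is untouched. The weakness lies in its stated safeguard, and it should be corrected.

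**What to change.** In 2.6.2, replace the sentence on the covariate with wording to this effect: if Bang's index indicates unblinding, the coil part of the guess (active v sham) and its interaction with Time will be added to the mixed model or, equivalently, the coil part will be a covariate in a model of the T0–T1 change. The adjusted T0–T1 rTMS and rTMS × DMI contrasts will be shown beside the unadjusted contrasts in the same participants. The result will be labelled a bounding analysis, because the guess is taken after treatment.

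This costs one or two sentences and no new data. The adjusted intervals will be wider, and the estimate may be over-adjusted where the guess reflects perceived improvement. The stated reason for the guess, already collected, can help in reading it.
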